### Setting

The study will be conducted in the general ICU of a tertiary level university hospital (Hospital das Clínicas at the University of São Paulo) in São Paulo, Brazil. The unit has a physiotherapist available at all times, and patients receive physical therapy twice a day. The patients receive respiratory care and mobilization from physical therapy professionals. There are no physiotherapy protocols in the unit; the protocol described in this article will be added to the physiotherapy routine for this research. The ICU is a general unit that receives patients with all kinds of illness as well as clinical and surgical patients. The average stay in the ICU is 12 days, and there are 14 beds.

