### Participants

Participants will be patients admitted to the ICU who are 18 years old or older with a Barthel Index equal to 100 points before hospitalization, who have not been transferred from another hospital, and who meet the criteria for inclusion in the progressive mobilization program will be enrolled in the study. The criteria for for initiation and continuity the progressive mobilization program follow the safety consensus described in the academic literature [19] and some points are as follows: respiratory rate (RR) ≤ 35 breaths per min, absence of cardiac arrhythmias or acute ischemia, heart rate (HR) between 50 and 140 beats per min, without the use of vasoactive drugs or without dose increase, mean arterial pressure (MAP) between 60 and 120 mmHg, absence of active bleeding, and no prescription of bed rest. Patients with MV with inspired fraction of inspired oxygen (FiO_2_) ≤ 60% and positive end-expiratory pressure (PEEP) ≤ 10 cmH_2_O are also eligible to participate.

Patients to be excluded include patients with neurological diagnoses associated with motor alterations, who refuse to carry out the proposed exercises or ask to withdraw less than 3 days after beginning the protocol, with contraindications for movement, those with pre-existing amputations or who undergo amputation upon hospitalization, and those who die before the final evaluation will be excluded from the study.

After admission to the ICU, patients will be evaluated at all times of the day regarding the inclusion criteria in the program. Patients will be evaluated within 2 days of admission to the ICU to participate in the study. If they do not present the criteria for initiating a mobilization program in that period [19], they will not be randomized and will not be included in the study.

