#### Patient assessment procedures

At the time of admission to the ICU and up to 2 days after admission, the patient will be examined against the inclusion criteria. The patient’s functionality in the 2 weeks before admission will be evaluated with the Barthel Index, which will be assessed by directly questioning the patient or their caregiver if they are unable to respond. Evaluation will include hemodynamic, respiratory, and cardiac stability for the safe practice of early mobility, and the absence of exclusion criteria will also be assessed. The patient will then be randomly placed in the control group or the intervention group.

After the patient is enrolled in the study, the initial variables will be collected, consisting of data related to the patient and their hospitalized and pre-hospitalization levels of functionality. At that time, an accelerometer will be placed on the patient to monitor their level of physical activity during the entire stay in the ICU.

Data on the patient’s hospitalization and the evolution of their condition, as well as the level of physical activity performed, will be collected during the entire stay in the hospital.

Upon discharge from the ICU or within 2 days of discharge, all patients will undergo a complete evaluation of their respiratory, muscular, and functional systems through methods already described in the academic literature and performed by a blind evaluator. The accelerometer will be removed, and the data will be analyzed in a dedicated computer program. Figure 2 shows a flowchart presenting the methods used in the study.

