### Primary and secondary outcome measures and assessment points

The outcome variables of the study will be respiratory, muscular, and functional variables; the length of stay in the ICU; and analyzed variables of physical activity, measured by the accelerometer.

The primary outcome will be the functional status at discharge from the ICU. The functional status is the difference between baseline and final score on both the Barthel Index and the IMS. Therefore, at discharge from the ICU, the Barthel Index and IMS will be redone, and the quantitative final score on those scales will be considered as the primary endpoints of the study. The secondary outcomes will be the respiratory and muscular variables and the number of days of hospitalization in the ICU. Further secondary outcomes will be the variables of physical activity performed during this period, which include an analysis of the intensity levels of the exercise to which the patient was submitted and the percentage of time spent sitting, lying, and standing.

For both groups, the occurrence of any adverse events related to motor therapy, such as respiratory or hemodynamic instability, accidental removal of invasive devices, falls, or pain will be recorded. Figure 3 illustrates the schedule of enrollment, allocation, intervention, and assessment of the study.

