### Statistical analysis including sample size calculations

Analyses for all aims will be performed according to the intention-to-treat paradigm. Comparative analysis between the control group and the intervention group will be performed for all outcome variables. For the comparison of the physiological variables and the levels of activity between the groups, a statistical test will be used to compare the two independent groups. For parametric data, the *t* test will be used.

To calculate the sample size for the primary outcome, we based the design on results found in Schweickert (2009) for a clinical trial. To an estimated expected difference in means in the primary outcome (Barthel Index score) of 13 points and a standard deviation of 22 points. Considering a statistical power of 80% and an alpha error of 0.5, we found that the number of subjects should be 48 per group, totaling 96 patients in the study.

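### ICU length of stay is a raw day count compared, by the exclusion rule, among ICU survivors only; that conflicts with intention to treat, and either reading is distorted if mortality differs between arms

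*Protocol article*

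**What the plan says.** All references are to the protocol article.

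- **Outcome** (Primary and secondary outcome measures and assessment points): "The secondary outcomes will be the respiratory and muscular variables and the number of days of hospitalization in the ICU". No value is assigned to the stay of a patient who dies.
- **Who is removed** (Participants): "those who die before the final evaluation will be excluded from the study".
- **When the final evaluation takes place** (Patient assessment procedures): "Upon discharge from the ICU or within 2 days of discharge, all patients will undergo a complete evaluation". Every death in the ICU therefore precedes it.
- **Analysis population** (Statistical analysis including sample size calculations): "Analyses for all aims will be performed according to the intention-to-treat paradigm".
- **Comparison** (same section): "Comparative analysis between the control group and the intervention group will be performed for all outcome variables", which includes ICU days. The only test named there is conditional on the data: "For parametric data, the *t* test will be used".
- **Typical stay** (Setting): "The average stay in the ICU is 12 days".

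The Background lists fewer ICU days among the reported benefits of early mobility, so a lower count will be read as a benefit.

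**The concern.** An ICU stay can end in live discharge or in death, and a day count does not tell them apart. The protocol gives two instructions about deaths, and neither yields a sound comparison of stay.

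- **If the exclusion rule governs**, ICU deaths contribute no stay. The arms are compared among patients who lived to be evaluated, and treatment can influence who those are. The protection of randomisation is lost for this outcome.
- **If intention to treat governs**, the deaths return, and a patient who dies on day 3 contributes 3 days, the same as one who recovers and leaves on day 3.

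At stake is the direction of the result. A programme that prevented deaths could appear to lengthen the stay, and one that caused deaths could appear to shorten it. Choosing between the two instructions settles who is analysed but does not by itself remove the problem.

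**Working it through.** **Plan's own figures.** The protocol gives no planned difference in length of stay and no mortality. Its 48 per group was calculated for the Barthel Index and is used here only for a standard error.

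**Inputs**
- Mean stay of 12 days in control (Setting; a figure for the whole unit).
- ICU mortality m = 10%, 25% and 30%: assumed, not in the documents.
- Constant daily hazards and an unchanged rate of live discharge: assumed.
- Death rate multiplied by 0.5 or 1.5 in the intervention arm: assumed, for illustration.

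**Step 1: mean stay.** In control the total exit rate is 1/12 per day, made up of m/12 for death and (1 − m)/12 for live discharge. Multiplying the death rate by k gives a mean stay of 12 / (1 − m + k·m).

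| m | k = 0.5: 12/(1 − m/2) | Change, days | k = 1.5: 12/(1 + m/2) | Change, days |
|---|---|---|---|---|
| 10% | 12.63 | +0.63 | 11.43 | −0.57 |
| 25% | 13.71 | +1.71 | 10.67 | −1.33 |
| 30% | 14.12 | +2.12 | 10.43 | −1.57 |

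With k = 1 the change is zero.

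**Step 2: deaths kept or dropped.** With constant hazards, the time of exit is independent of the kind of exit, so the survivors' mean equals the overall mean and the table applies to both readings. That equality belongs to the model. A simulation with 20% baseline mortality added a shared severity effect (SD 0.5 on both log hazards, delaying discharge and hastening death). With the death rate halved, unchanged and doubled, mean stay was:
- deaths kept: 13.4, 11.5 and 9.2 days;
- deaths dropped: 12.9, 11.0 and 8.9 days.

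The values differ between the two readings, but the direction is the same.

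**Step 3: alternatives at m = 25% with the death rate halved**
- *Live discharge by day 28, death competing.* Control: 0.75 × (1 − e^(−28/12)) = 0.75 × 0.903 = 67.7%. Intervention: the share discharged alive is 0.75/0.875 = 0.857, and 0.857 × (1 − e^(−28 × 0.875/12)) = 0.857 × 0.870 = 74.6%.
- *Days alive and out of the ICU to day 28.* Control: 0.75 × [28 − 12 × 0.903] = 12.9. Intervention: 0.857 × [28 − 13.71 × 0.870] = 13.8. Deaths after ICU discharge are ignored.

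Both measures improve, while raw ICU days go from 12.0 to 13.7 and look worse.

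**Step 4: size against noise.** Under the exponential model the SD equals the mean, 12 days. With 48 per arm, the standard error of the difference is 12 × √(2/48) = 2.4 days. Every change in the table is smaller than this.

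**The case against.** A reader might infer that the protocol scores a death as a short, favourable stay. As written it does not: the exclusion rule removes the patient. That reading applies only if the intention-to-treat statement overrides the exclusion. This objection stands, and the defect under the written rule is a survivors-only comparison.

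A reader might also infer that the result for stay will come out reversed. The documents do not support that. No passage expects an effect on mortality, and the benefits listed in the Background do not include one. With equal death rates the model shows no distortion. The mortality range is assumed, and halving the death rate or raising it by half is a large effect. The 12-day mean describes the whole unit, whereas trial patients are selected: fully independent before admission and stable enough to start mobilisation within 2 days. The shifts are also smaller than one standard error. All of this stands and limits the weight of the point.

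It can further be said that competing-event handling of a secondary outcome belongs in an analysis plan that is not shown, and that the root problem is the exclusion of deaths, which affects the primary outcome first. The choice of test may indeed sit elsewhere. The exclusion of deaths, its conflict with intention to treat and the day count are fixed in this article, however, and resolving the conflict either way leaves the stay comparison open to distortion.

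Finally, it would be too strong to say that length of stay must be abandoned. Time to live ICU discharge keeps the same clinical question and changes the analysis.

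**Conclusion.** The point holds. By its exclusion rule the protocol compares ICU days among survivors, contrary to intention to treat for all aims. If deaths are kept instead, raw days count an early death as a short stay. Under both readings a between-arm difference in mortality distorts the comparison: more survival lengthens the stay and less survival shortens it.

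The illustrative size is about +0.6 to +2.1 days for a halved death rate and −0.6 to −1.6 days for one raised by half. This rests on constant hazards, a 12-day mean, assumed mortality of 10% to 30% and an unchanged rate of live discharge. The conflict between the passages and the direction of the distortion are firmer than these sizes. Because this is a secondary outcome and no mortality effect is posited, the importance is low to moderate.

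**What to change.** 1. Reconcile the Participants section with the statistical section: keep every randomised patient, including those who die, in the length-of-stay analysis.
2. Analyse time from randomisation to live ICU discharge with death as a competing event, shown as cumulative incidence by arm. Alternatively, use ICU-free days to a fixed day after randomisation (for example day 28), compared by a rank test with death given the worst rank. Death should rank below being alive but still in the ICU at that day; otherwise the two tie at zero (in the model, e^(−28/12), or about 10% of control patients, are still there).
3. Report ICU deaths by arm beside this outcome.
4. Give raw ICU days in survivors as description only.

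The cost is mainly wording, plus keeping ICU discharge and death dates for patients the exclusion rule would have removed. Hospitalisation data are already collected throughout the hospital stay. The ICU-free-days option also needs vital status at the chosen day; the planned calls are at 3 months and 1 year after hospital discharge and concern the Barthel Index, so this would have to be added or taken from records. The summary is somewhat less direct than a mean number of days. The change should be made before the arms are compared.

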**Fig. 3 Fig3:**
[figure not shown]
Standard Protocol Items: Recommendations for Interventional Trials (SPIRIT) Figure, describing the schedule of the study

### Recruitment procedures

Patients will be recruited directly in the ICU at the time of admission to the unit. The criteria for inclusion in the study and the signing of informed consent for inclusion in the study will be analyzed. Data will be assessed only by the researchers and kept confidentially. Patients have been recruited since February 2017, and the expected completion date of the study is August 2018.

### Randomization procedures

Patients will be allocated to each group through computerized randomization. It will be a study of superiority, conducted in a single center. The patient allocation will be concealed, and the randomization of the individual will be performed by a researcher who is not involved in enrolling the participants, assigning them to groups, or performing follow-up measurements. This researcher will keep the allocation hidden in sealed brown envelopes within a box, which will be opened individually only at admission to the ICU when the participant is enrolled in the study. Individuals will be distributed between two groups. Only the researcher responsible for conducting the protocol will know how the participants are distributed.

### Masking/blinding

This is a blind evaluator study. The evaluator will not know the group to which the evaluated subject was assigned. Therefore, the patients will be instructed not to report their activity during hospitalization, and the equipment used in the protocol will be removed from the patient’s bed so that the evaluator cannot see the equipment that was used. The evaluator will also have no access to the tabulation of the split group data and will record the evaluation data on a separate worksheet.

### Statistical analysis including sample size calculations

Analyses for all aims will be performed according to the intention-to-treat paradigm. Comparative analysis between the control group and the intervention group will be performed for all outcome variables. For the comparison of the physiological variables and the levels of activity between the groups, a statistical test will be used to compare the two independent groups. For parametric data, the *t* test will be used.

To calculate the sample size for the primary outcome, we based the design on results found in Schweickert (2009) for a clinical trial. To an estimated expected difference in means in the primary outcome (Barthel Index score) of 13 points and a standard deviation of 22 points. Considering a statistical power of 80% and an alpha error of 0.5, we found that the number of subjects should be 48 per group, totaling 96 patients in the study.

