**Methods:**

This is a protocol for a randomized controlled trial with blind evaluation. Ninety-six ICU patients will be recruited from a single center and randomly assigned to a control group or an intervention group. To determine the level of protocol activity the patient will receive, the patients’ ability to participate actively and their muscle strength will be considered. The protocol consists of five phases, ranging from passive therapies to walking and climbing stairs. The primary outcome will be the functional status at ICU discharge, measured with the Barthel Index and the ICU Mobility Scale (IMS). Measured secondary outcomes will include the level of physical activity, maximal inspiratory and expiratory pressures, forced expiratory volume in 1 second, maximum voluntary ventilation, handgrip strength, surface electromyography of the lower limb muscles, and results of the Timed Up and Go and 2-Minute Walk tests. Evaluations will be made within 2 days of ICU discharge except for the level of activity, which will be evaluated daily. Physiological variables and activity level will be analyzed by chi-square and *t* tests, according to the intention-to-treat paradigm.

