**Fig. 2 Fig2:**
[figure not shown]
Flowchart of the study

Patients in both groups will use an Actigraph wGT3X-BT accelerometer (ActiGraph LLC®, Pensacola, FL, USA) throughout the length of their hospital stay, a tool which analyzes their position and level of activity. The accelerometer will be placed on the dominant lower limb using a bandage and will not be removed until discharge, allowing information on the patient’s physical activity to be collected objectively. The evaluation of the intensity of the exercises performed during ICU stay in both groups will be performed through the parameters evaluated by the accelerometer. This instrument is able to identify the intensity of the exercise performed, and for analysis we will divide it into mild, moderate and intense or absence of activity. Exercise intensity will also be monitored and evaluated by the Borg Scale at the end of each physical therapy session. At the end of the ICU stay, the equipment will provide data such as the exercise intensity and time spent lying down, sitting, and standing [24].

The following data concerning hospitalization will be collected: use of vasoactive drugs, use of corticoids or neuromuscular blockers, hypoglycemia, the presence of sepsis, surgery, hemodialysis, use of invasive and non-invasive MV, tracheostomy, and the number of days spent in the different therapies that were evaluated.

Evaluation of the respiratory system, muscular system, and functionality after ICU discharge will be performed by a blind evaluator using methods previously described in the academic literature. These data will be correlated with the physical activity data obtained from the accelerometer.

The respiratory evaluation will be performed using the maximal inspiratory pressure test with the use of a manovacuometer (Wika Corporate®, Klingenberg, Germany), while evaluation of pulmonary function will be done through spirometry, assessing the forced expiratory volume in 1 second (FEV_1_) and maximum voluntary ventilation [25] with a Datospir – Micro C digital spirometer (Sibelmed®, Barcelona, Spain).

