The muscular evaluation will be performed by measuring MS with a handgrip dynamometer (Jamar Enterprises LDT®, Hoddesdon, United Kingdom) [26]. Muscle activity will be measured by electromyography of three muscles in the lower limbs—the anterior tibial, medial gastrocnemius, and vastus lateralis muscles—using a Miotool Miotec device (Miotec Equipamentos Biomédicos Ltda®, Porto Alegre, Brazil). The patient will perform the voluntary contraction three times in each muscle, accompanied by an electrogoniometer (Miotec Equipamentos Biomédicos Ltda®, Porto Alegre, Brazil) [27, 28].

Muscular function and mobility will be evaluated using the Timed Up and Go test [29] and the 2-Minute Walk test [30].

Functionality will be evaluated using the Barthel Index [31], measured by directly questioning the patient and by using the ICU Mobility Scale (IMS) [32].

The demographic data and initial evaluation of the patient will be collected on a data sheet. The patient’s physical activity data will be collected by the accelerometer and stored in the equipment’s software, and will later be included in the general tabulation of patient data. The physical evaluation data (dynamometry, electromyography, respiratory MS, and spirometry) will be collected on the same data sheet.

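### Lung function, respiratory pressures and handgrip, listed only at ICU discharge, are compared by a valid but unadjusted two-group test, which gives up precision that sex, age and height could recover

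*Protocol article*

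**What the plan says.** - **Test.** The section on statistical analysis and sample size states: "For the comparison of the physiological variables and the levels of activity between the groups, a statistical test will be used to compare". Its objects of comparison are two independent groups, and it gives the t test for parametric data. The abstract agrees: "Physiological variables and activity level will be analyzed by chi-square and" t tests. Neither place names a covariate, and the randomization section names no stratification factor.
- **Timing.** Under patient assessment procedures: "Upon discharge from the ICU or within 2 days of discharge, all patients will undergo a complete evaluation of their respiratory, muscular, and functional systems". The abstract exempts only the activity level, which is recorded daily. The initial data are described as patient data and functional level. No baseline spirometry, pressure or handgrip value is listed, although the schedule figure is not shown.
- **Measures.** "The respiratory evaluation will be performed using the maximal inspiratory pressure test", followed by spirometry for FEV1 and maximum voluntary ventilation. For muscle: "The muscular evaluation will be performed by measuring MS with a handgrip dynamometer". The text does not say whether values are analysed in absolute units or as percent of predicted.
- **Covariates available.** "The demographic data and initial evaluation of the patient will be collected on a data sheet". The demographic items are not itemised.
- **Population and status.** Patients are 18 or older with no upper age limit, in a general ICU. The respiratory and muscular variables are secondary outcomes.

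**The concern.** With one listed measurement per patient, nobody serves as their own control. FEV1, maximum voluntary ventilation, maximal pressures and handgrip depend on sex, age and body size, and the eligible population spans all of these. A two-sample t test treats that predictable spread as noise, although demographic data are collected.

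What is at stake is power: a real respiratory or muscular benefit is more likely to be missed than the data require. The title and the discussion put these benefits among the aims of the trial, while the sample size was set on the Barthel Index alone. Precision for these outcomes therefore depends on how they are analysed. A lesser issue is that, if one arm happens to contain many more men, the unadjusted difference in that particular trial is misleading.

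**Working it through.** **1. The plan's own figure.** Inputs from the sample size section: difference 13 points, SD 22, power 80%, 48 per group. Alpha is printed as 0.5 and is read here as 0.05, two-sided (0.5 would need only 14 per group).

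n per group = 2 × [22 × (1.96 + 0.842) / 13]² = 44.96, so 45. The t-based calculation gives 46. Power at 48 per group is 81.7% (t-based). The stated 48 is thus reproduced to within 2 patients. It concerns the Barthel Index only; no power is stated for the outcomes discussed here.

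**2. Unadjusted precision at 48 per arm.** In SD units the standard error of the arm difference is √(2/48) = 0.204. The difference detectable with 80% power (t-based, two-sided 0.05) is 0.578 SD.

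**3. Effect of adjustment.** Let R² be the share of outcome variance explained by sex, age and body size. The documents give no value, so 0.1 to 0.6 is an assumption. The standard error is multiplied by √(1 − R²), the detectable difference is 0.578 × √(1 − R²), and the equivalent number per arm for an unadjusted test is 48 / (1 − R²). Power for a true difference of 0.4 SD is Φ(0.4 / [0.204 × √(1 − R²)] − 1.96).

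| R² | SE factor | SE cut | Detectable difference (SD) | Equivalent n per arm | Power at 0.4 SD |
|---|---|---|---|---|---|
| 0 (t test) | 1.000 | – | 0.578 | 48 | 50% |
| 0.1 | 0.949 | 5% | 0.548 | 53 | 54% |
| 0.2 | 0.894 | 11% | 0.517 | 60 | 59% |
| 0.3 | 0.837 | 16% | 0.483 | 69 | 65% |
| 0.5 | 0.707 | 29% | 0.409 | 96 | 79% |
| 0.6 | 0.632 | 37% | 0.365 | 120 | 87% |

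The table ignores the small cost of estimating three slopes. For roughly normal covariates that cost is a variance factor of about 1 + 3/(96 − 3 − 3) = 1.033, or 1.6% on the standard error. It matters only at the bottom of the range. The table also assumes that all 48 per arm are measured. The protocol excludes patients who die before the final evaluation and states no allowance for losses, so fewer may contribute.

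**4. Chance imbalance.** With 48 per arm and half the patients men (assumed), exact binomial calculation gives a difference in the share of men of at least 10 points in 36% of trials and at least 20 points in 5%.

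Simulating the unadjusted t test with no treatment effect:
- Over all randomizations, the false-positive rate is 4.9% at R² 0.3, 0.5 and 0.7.
- Given a covariate imbalance beyond 1.96 standard errors, it is 21%, 33% and 47% at those R² values. Given an imbalance under 1 standard error, it is 2.6%, 1.4% and 0.4%.
- For sex alone, with an assumed gap of 1 or 1.5 SD between men and women, 5 more men in one arm (10.4 points) gives 4.9% or about 3.5%, which is not above nominal. Eight more men gives about 9% or 13%.

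A 10-point imbalance shifts the arm difference by 0.10 to 0.15 SD under those assumed gaps. That is 0.5 to 0.7 of the 0.204 standard error.

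**The case against.** The strongest reply is that the stated test is valid, that covariates for secondary outcomes are ordinarily left to an analysis plan, and that a condensed article does not exclude them. The first part stands. The second stands only in part: the article does not merely omit the analysis, it names the test in two places, and for these outcomes a better one is available at almost no cost.

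Three stronger readings are tempting, and the documents do not support them.

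- *Raw values are compared.* A reader might infer this because no scaling is mentioned. The text is equally compatible with percent of predicted for the lung-function measures.
- *A sex imbalance will be reported as a treatment effect.* The overall error rate of the t test already includes chance imbalance and stays at 5%. Moderate imbalances of about 10 points, which occur in roughly one trial in three, do not raise false positives above nominal in the simulation. Only marked imbalances do, and those are uncommon.
- *The discharge comparison is the only use of these measurements.* The protocol also plans to correlate them with the accelerometer data.

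It is also fair to say that R² may be low here. The background section attributes muscle dysfunction in the ICU to inflammation, drugs, immobility and neuromuscular syndromes, so illness itself may supply much of the variance at discharge. That is why the range above starts at 0.1, where the gain is small.

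**Conclusion.** The point holds as a cheap gain in efficiency. It does not show an invalid analysis. The documents establish an unadjusted two-group test as the only named method, outcomes described at ICU discharge without a listed baseline, a wide adult population, and demographic data on the data sheet.

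The size rests on an assumed R². From 0.1 to 0.6, the detectable difference at 48 per arm falls from 0.58 SD to between 0.55 and 0.37 SD, a gain that runs from marginal to substantial. Adjustment would also remove the conditional distortion in a trial where a marked imbalance has occurred in the covariates used. Two limits remain: the schedule figure could show a baseline measurement that the text does not mention, and the demographic items are not listed. The primary Barthel Index and ICU Mobility Scale result and the sample size are untouched.

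**What to change.** Before unblinding, replace the t test for FEV1, maximum voluntary ventilation, maximal respiratory pressures and handgrip with a linear model containing arm, sex and age, and height if it was recorded. Report the adjusted difference with its 95% interval, and keep unadjusted means by arm as description. State the measurement scale of each outcome. Percent of predicted for the lung-function measures is a workable alternative but not an equivalent, because it imposes external reference equations instead of estimating the covariate effects in these patients.

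The cost is analysis wording and a check of which demographic items are on the data sheet. No visit, measurement or patient is added. The one small downside is a model in place of a t test.

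### The printed alpha of 0.5 cannot give 48 per group; two-sided 0.05 does, and the resulting power has a margin of only 2 or 3 patients per group

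*Protocol article*

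**What the plan says.** The section Statistical analysis including sample size calculations assumes an "expected difference in means in the primary outcome (Barthel Index score) of 13 points" and "a standard deviation of 22 points". It then gives power, alpha and result in one sentence: "Considering a statistical power of 80% and an alpha error of 0.5, we found that the number of subjects should be 48 per group". The total is 96. For parametric data the planned comparison is a t test.

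Sidedness is not stated. The section Randomization procedures says only: "It will be a study of superiority, conducted in a single center". No other part of the article gives a significance level.

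The Methods part of the Abstract says that ninety-six patients will be recruited and randomly assigned, so the calculated number and the randomised number are the same. The Participants section removes some patients after entry: "those who die before the final evaluation will be excluded from the study". It also removes those who refuse the exercises or withdraw in the first days of the protocol, and those who have an amputation during the hospital stay. The Intervention group section adds a further exclusion during the ICU stay. The article gives no expected loss rate and no replacement rule, and it also says that all analyses follow intention to treat.

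**The concern.** All the inputs to the sample size are printed together, so the paragraph can be checked against itself. An alpha of 0.5 is far from any conventional threshold and should lead to a much smaller trial than 48 per group. Because no other passage states a significance level, nothing in the article corrects the figure, and a reader cannot cite the trial's error rate from it.

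The second matter is what the 80% refers to. If 48 is the number randomised and the plan takes patients out before the discharge assessment, the stated power applies to a number of patients that the analysis may not have.

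**Working it through.** **Inputs.** Difference 13, SD 22, power 80%, two equal groups, t test, 48 per group: all from the sample-size section. Alpha is printed as 0.5. Sidedness is not stated, so both were tried.

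**Formula (normal approximation).** n per group = 2 × (z_alpha + z_0.80)² × (22/13)², where z_alpha is z_(1−alpha/2) two-sided or z_(1−alpha) one-sided. Here (22/13)² = 2.864, so the multiplier is 2 × 2.864 = 5.728, and z_0.80 = 0.842. The t-test figures use the noncentral t distribution with effect size 13/22.

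**Step 1: try to reproduce 48.**

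| Alpha | Sides | Normal formula | t test | Power at 48 per group |
|---|---|---|---|---|
| 0.5 (as printed) | two | 5.728 × (0.674 + 0.842)² = 13.17, so 14 | 12.31, so 13 | 98.7% |
| 0.5 (as printed) | one | 5.728 × (0 + 0.842)² = 4.06, so 5 | 4.06, so 5 | 99.8% |
| 0.05 | one | 5.728 × (1.645 + 0.842)² = 35.4, so 36 | 36.1, so 37 | 89.4% normal, 89.0% t |
| 0.05 | two | 5.728 × (1.960 + 0.842)² = 44.96, so 45 | 45.94, so 46 | 82.5% normal, 81.7% t |

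Neither alpha 0.5 row comes near 48. Only two-sided 0.05 does, to within 2 patients (t test) or 3 (normal formula). An unstated 5% allowance on the normal figure would give 48 after rounding up: 45/0.95 = 47.4.

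**Step 2: the margin at two-sided 0.05.**

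| Evaluable per group | Power, normal | Power, t test |
|---|---|---|
| 48 | 82.5% | 81.7% |
| 47 | 81.7% | 80.9% |
| 46 | 80.9% | 80.1% |
| 45 | 80.0% | 79.2% |
| 44 | 79.2% | 78.2% |

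Power stays at 80% after the loss of 2 per group by the t test (2/48 = 4.2%) or 3 per group by the normal formula (3/48 = 6.3%).

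**Step 3: power under loss.** The article gives no loss rate, so the rates below are assumptions. Difference and SD are kept at 13 and 22.

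| Assumed loss | 48 × (1 − loss) | Power, normal | Power, t test |
|---|---|---|---|
| 5% | 45.6 | 80.6% | 79.7% |
| 10% | 43.2 | 78.4% | 77.5% |
| 20% | 38.4 | 73.5% | 72.4% |
| 30% | 33.6 | 67.8% | 66.5% |

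With whole patients (43, 38 and 34 per group) the t-test figures are 77.3%, 72.0% and 67.0%.

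**The case against.** The strongest reply is that this is a dropped zero with no effect on the design. The sample size, the recruitment target and the planned t test are unchanged once the digit is corrected, and the other inputs show that 0.05 was used. That stands, and it limits the consequence. A reader might infer that the trial accepts a false-positive rate of one in two. The article does not support this: 0.5 appears only as an input to the sample size, no passage says that results will be judged at that level, and the 48 per group shows that the calculation did not use it. What remains is that the only printed error rate is wrong and nothing else in the article corrects it.

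On losses, a condensed article may leave a dropout allowance or a replacement rule to the full protocol, and an allowance of about 5% may already be inside the 48. Participants must also be fully independent before admission and meet stability criteria within 2 days, so the mortality of the unit as a whole may not apply to them. These points stand, and they make the matter secondary. They do not enlarge the margin: a silent 5% allowance is the same 2 or 3 patients per group shown above.

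A reader might also infer that intention to treat settles the matter because all 96 are analysed. The article does not support that either. The Participants section takes deaths out, and a patient who dies before ICU discharge has no discharge Barthel or ICU Mobility Scale score. Deleting the exclusion would not supply one. If deaths were given a score, the SD of 22 and the 13-point difference might no longer hold. How the exclusions fit with intention to treat is a separate question of bias, beyond this point about power.

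**Conclusion.** The point holds. The alpha of 0.5 is wrong as printed: it implies about 13 to 14 per group (two-sided), not 48. It is evidently a misprint for two-sided 0.05, which needs 45 (normal formula) or 46 (t test) and gives 81.7% power at 48 by the t test. This part rests only on the article's own numbers. A reader might go further and call the sample size itself wrong. It is not: 48 per group is adequate for complete data under the stated assumptions.

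The secondary part is weaker. No allowance for loss is visible, and the margin is 2 or 3 patients per group. How far power falls depends on a loss rate that the article does not give; about 77%, 72% and 67% (t test) correspond to assumed losses of 10%, 20% and 30%.

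**What to change.** 1. In the sample-size section, replace 0.5 with two-sided 0.05.
2. State there that 80% power needs 46 evaluable patients per group by the t test, and that 48 per group gives 81.7% with complete data.
3. State the expected number of evaluable patients, after the deaths and early withdrawals that the Participants section excludes, and restate the power for that number. If the 48 already includes an allowance, say so and give its size.
4. Do not claim that all 96 will be analysed unless a rule for scoring patients who die before discharge is also given. With such a rule, revisit the assumed difference and SD.

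The cost is a change of wording. No extra enrolment is needed. The stated power may become somewhat less favourable, and recruitment was still open according to the Trial status section.
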